### Clinical Outcomes (Aim 1)

The primary clinical outcome is safety or frequency of SAEs. The secondary clinical outcome is the patients’ stroke severity (measured by NIHSS) and the level of disability (measured by modified Rankin scale) at 1 week and 90 days. The modified Rankin scale is a widely used tool for measuring outcome in stroke trials. A score of 0 indicates no disability and 6 indicates death. Neurological impairment and functional scores will be measured by a neurologist. The NIHSS will be assessed before the acute study, then again at 24 h, at time points coinciding with MRI scanning (1 week, 1 month, and 12 months), and at any other time during the hospital stay if there is a clinical deterioration. *The neurological and safety outcome assessment will therefore be performed by a blinded observer. This observer will not be involved in patient recruitment*.

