### Imaging Outcomes

The primary imaging outcome is the volume of vasogenic edema at 1 week versus that before treatment. This analysis is performed with a view to assessing safety. The secondary imaging outcome is the change in the infarct expansion ratio (IER) between the outcome post-treatment (T2 FLAIR) infarct volume and the initial DWI infarct volume (see Image Analysis) (16), and symptomatic intracerebral hemorrhage on MR or CT (4). Symptomatic intracerebral hemorrhage is defined by Safe Implementation of Thrombolysis in Stroke Monitoring Study (SIT-MOST) criteria as parenchymal hematoma type 2 (PH2) occurring within 3–6 hours of treatment, combined with neurological deterioration leading to an increase of four points on the NIHSS from baseline, or the lowest NIHSS value after baseline to 24 h (24).

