### Imaging Protocol

Patients will have MR imaging performed prior to receiving hAECs and at 1 week, 1 month, and at 12 months. The sequences include volumetric 3D T1 images, T2 weighted FLAIR images, DWI (measures infarct volume) and tensor imaging/DTI (assesses integrity of white matter tracts), MR angiography (assesses blood vessel patency), arterial spin labeling (assesses cerebral blood flow), and susceptibility weighted imaging (detection of blood products). The choice of these MR sequences is based on consensus recommendations from an expert panel: Stem Cells as an Emerging Paradigm in Stroke (STEPS) 3 (8).

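### The 3–6 h symptomatic hemorrhage window fits neither its own 24 h NIHSS reference nor the assessment schedule, and the NIHSS visit list has no 90-day entry

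*Protocol article*

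**What the plan says.** **Hemorrhage.** The protocol article (Imaging Outcomes) makes symptomatic intracerebral hemorrhage, seen on MR or CT, a secondary imaging outcome. It is defined as "parenchymal hematoma type 2 (PH2) occurring within 3–6 hours of treatment", together with neurological deterioration amounting to "an increase of four points on the NIHSS from baseline, or the lowest NIHSS value after baseline to 24 h". The Imaging Protocol section sets the scans: "Patients will have MR imaging performed prior to receiving hAECs and at 1 week, 1 month, and at 12 months". No CT time is given.

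**NIHSS and disability.** Clinical Outcomes (Aim 1) names stroke severity on the NIHSS and "the level of disability (measured by modified Rankin scale) at 1 week and 90 days" as the secondary clinical outcome. The same section then lists the NIHSS times: "The NIHSS will be assessed before the acute study, then again at 24 h", then "at time points coinciding with MRI scanning (1 week, 1 month, and 12 months", and in addition whenever an inpatient deteriorates.

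**Safety net.** Clinical Outcomes makes SAE frequency the primary outcome, and the Safety section equates DLT with SAE.

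**The concern.** Both outcomes are tied to times that the rest of the text does not support.

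(a) The hemorrhage window closes at 6 h. The NIHSS reference in the same sentence may be a value reached as late as 24 h, and nothing is scheduled inside the window. A hematoma that is large, symptomatic and plainly relevant to safety could be excluded from the named outcome only because it occurred at 12 h or on day 3. The 1-week MRI includes susceptibility weighted imaging to detect blood products, yet a bleed it shows with onset outside the window cannot be counted. The reported hemorrhage figure would then be too low for what its name promises.

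(b) On the natural reading, NIHSS at 90 days is a secondary outcome without a matching visit in the section's own NIHSS list. Sites cannot follow both sentences as they stand.

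**Working it through.** The protocol states no figure to reproduce on this point. The check compares outcome times with assessment times, followed by a sensitivity calculation under stated assumptions.

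**Step 1: times side by side**

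| Item | Times stated | Source |
|---|---|---|
| PH2 window | 3–6 h | Imaging Outcomes |
| NIHSS reference for the four-point rise | baseline, or lowest value up to 24 h | Imaging Outcomes |
| MRI | before treatment, 1 week, 1 month, 12 months | Imaging Protocol |
| NIHSS visits | before treatment, 24 h, 1 week, 1 month, 12 months, in-hospital deterioration | Clinical Outcomes |
| Secondary clinical outcome | 1 week, 90 days | Clinical Outcomes |

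**Step 2: what falls in the hemorrhage window**

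- Scheduled post-treatment MRI inside 3–6 h: 0 of 3. The earliest is at 7 × 24 = 168 h.
- Scheduled post-treatment NIHSS inside 3–6 h: 0 of 4. The earliest is at 24 h, which is 24 − 6 = 18 h after the window closes.
- The window covers 3/168 = 1.8% of the time from treatment to the first follow-up MRI. This is a share of clock time, not of bleeds.

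**Step 3: share of bleeds inside the window (assumed onset)**

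The protocol has no data on bleed timing, so two families of onset distribution are tried over a period of T hours after treatment.

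- Uniform onset: share = 3/T. This gives 12.5% for T = 24, 8.3% for T = 36, 4.2% for T = 72 and 1.8% for T = 168.
- Exponential onset with half-time h, truncated at T: λ = ln 2/h, share = (e^(−3λ) − e^(−6λ))/(1 − e^(−Tλ)).
  - h = 6, T = 24: (0.7071 − 0.5000)/(1 − 0.0625) = 0.2071/0.9375 = 22.1%, the highest value found.
  - h = 48, T = 168: (0.9576 − 0.9170)/(1 − 0.0884) = 0.0406/0.9116 = 4.5%, the lowest in this family.

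The overall range is about 2–22%.

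**Step 4: the wording read as an upper limit**

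If the phrase means any time up to 6 h, the numerator becomes 6 h.

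- Uniform: 6/168 = 3.6% to 6/24 = 25%.
- Exponential, h = 6, T = 24: (1 − 0.5)/0.9375 = 53%.

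The share is therefore sensitive both to the reading and to the assumed onset. Under either reading, bleeds at 12 h and on day 3 are outside.

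**Step 5: the 90-day outcome**

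The NIHSS list contains 1 week but not 90 days. Taking 1 month as 30 days and 12 months as 365, the nearest visits are 90 − 30 = 60 days earlier and 365 − 90 = 275 days later.

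**The case against.** Five points can be made for the protocol.

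1. **Symptomatic bleeds are found through symptoms.** An inpatient who deteriorates gets an unscheduled NIHSS, and allowing CT without scheduling one suggests clinically prompted imaging. This stands: the lack of a routine scan or NIHSS at 3–6 h is not in itself a defect, and a bleed inside the window could be caught. It does not rescue a bleed at 12 h, which may be detected and is still not counted.
2. **Safety decisions do not depend on this outcome.** A PH2 at any time that is fatal, life threatening, prolongs the stay or otherwise meets the SAE definition enters the primary outcome and the DLT count. This stands and limits the damage to one secondary outcome.
3. **The 24 h phrase sets a reference value, not a window.** That is correct, so the sentence is not a strict logical contradiction. It is still a poor fit: a lowest value reached after 6 h cannot serve as the reference for a worsening with a bleed confined to the first 6 h.
4. **The 90 days may belong to the Rankin scale alone.** The grammar permits this. If it is what was meant, the sentence needs to say so, and the NIHSS outcome needs its own time.
5. **An article condenses the full protocol.** Here, however, the article states both sets of times and they do not match. A fuller visit table could show which was intended, but could not make both statements true.

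A reader might also infer that most bleeds are missed, or that the hemorrhage count will be near zero whatever the treatment does. The documents give no bleed timing, so neither can be asserted.

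**Conclusion.** The point holds as a mismatch between outcome definitions and the stated assessments, in two parts.

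(a) As written, the symptomatic hemorrhage outcome leaves out PH2 with a four-point worsening after 6 h and would under-report. The extent is unknown. The 2–22% range rests on assumed uniform or exponential onset and on reading the window as 3 to 6 h. The effect is confined to a secondary imaging outcome; events that qualify as SAEs still reach the primary outcome and dose decisions. What the cited criteria specify could not be checked and plays no part in this conclusion.

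(b) The 90-day NIHSS outcome has no counterpart in the NIHSS visit list, unless 90 days was meant for the Rankin scale only.

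Two stronger readings of (b) are not supported. It does not follow that 90-day data will never be collected: the outcome sentence itself names the time, the visit list covers the NIHSS only and so says nothing about the Rankin scale, and follow-up runs to 12 months. Nor does the gap undermine a comparison with the 15.7% 90-day mortality in Sample Size. The protocol uses that figure only as context for the 0.3 target rate and plans no such comparison.

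Both parts should be corrected before recruitment. Neither threatens the determination of the MTD.

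**What to change.** **(a) Imaging Outcomes.** Check the hemorrhage window against the cited criteria and restate it so that it agrees with the 24 h NIHSS reference in the same sentence. In addition, tabulate every PH2 with a four-point NIHSS worsening from the start of infusion through the 1-week MRI, whether seen on the scheduled MR or on clinically prompted CT or MR. The MR sequences needed are already planned, so this costs wording and one table row, with no extra scans.

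**(b) Clinical Outcomes.** Reconcile the two sentences in one of two ways:

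- add 90 days to the list of NIHSS times; or
- state that 90 days applies to the modified Rankin scale only, and name the NIHSS outcome at times already scheduled, keeping 1 week.

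The first option costs at most one 90-day assessment per patient, 15 in total. The second costs only wording.

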### Imaging Protocol

Patients will have MR imaging performed prior to receiving hAECs and at 1 week, 1 month, and at 12 months. The sequences include volumetric 3D T1 images, T2 weighted FLAIR images, DWI (measures infarct volume) and tensor imaging/DTI (assesses integrity of white matter tracts), MR angiography (assesses blood vessel patency), arterial spin labeling (assesses cerebral blood flow), and susceptibility weighted imaging (detection of blood products). The choice of these MR sequences is based on consensus recommendations from an expert panel: Stem Cells as an Emerging Paradigm in Stroke (STEPS) 3 (8).

### Image Analysis

Images will be de-identified prior to analysis. The analysis will therefore be performed blinded to the dosing regiments. Segmentation of infarct will be performed using in-house purpose-written semi-automated software. In a previous analysis from our group, the IER in the control arm occurred in 75% of patients (16). Hyperintense signal on FLAIR images consists of the infarct (cytotoxic edema) and surrounding vasogenic edema. By contrast, the lesion on DWI consists of cytotoxic but not vasogenic edema. Vasogenic edema is therefore defined as the difference between the hyperintense signal on FLAIR sequence at day 7 minus the hyperintense signal on the DWI sequence (all sequences will be co-registered to the same coordinate space for analysis). The DTI images will be used to characterize longitudinal change in the fractional anisotropy (white matter integrity) around the infarct. Used in this way, it will provide another measure of peri-infarct injury and/or recovery.

### Immunological Assay

We will perform studies to evaluate the effects of the hAECs on the immune response post stroke. Assessments will be made before hAEC administration, 1 h after hAEC infusion, and at 24 h, 3 days, and 1 week. Venepuncture will be performed using EDTA tubes at the time of enrollment and transported to the laboratory. We will measure the following:
Lymphocytes: circulating T lymphocytes (CD4^+^, CD8^+^), CD56^+^ natural killer cells, CD19^+^ B cells, and T regulatory cells.Key cytokines and markers of inflammation: IFNγ, TNFα, IL-10, IL-17, IL-6, high-sensitivity C-reactive protein.BBB integrity: MMP-9 (9).Immunogenicity: HLA typing of hAEC and recipient.

## Results

The expected outcome from Aim 1 is the MTD to inform the dose to be used in a Phase 2 trial. A smaller vasogenic edema volume, a decrement in infarct expansion, and a decrement in fractional anisotropy volume with dose escalation will provide another assessment of safety and efficacy. It is expected that at the MTD, infarct expansion will be lower than at the preceding doses and in the control group. The immunological assays should parallel our findings in animal experiments (e.g., dampening of the pro-inflammatory cytokines). The findings of the study will be submitted for publication in peer-reviewed journals. Following this, the application will be made to the National Health Medical Research Council to obtain funding for Phase 2 trial.

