## Method

### Overall Plan

We have designed an open label Phase 1 dose escalation trial of hAECs in patients with ischemic stroke with the primary aim of determining the maximal tolerated dose (MTD). Assessment of adverse events will be undertaken blinded to cell dose. Fifteen patients will be recruited for a dose escalation trial in 2018. The final follow-up for the 15th patient in the hAEC arm will be done 12 months after cell delivery. The trial will be submitted to the Monash Health Human Research Ethics Committee.

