### Treatment Doses

Treatment doses are of stage-wise dose escalation: 2, 4, 8, 16, and 32 million cells/kg.

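### Results expects less infarct expansion at the MTD than in a control group that this trial does not have; the dose contrast is very imprecise and the favourable direction for anisotropy is unclear

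*Protocol article*

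**What the plan says.** All references are to the protocol article.

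- **Design.** Overall Plan: "We have designed an open label Phase 1 dose escalation trial of hAECs in patients with ischemic stroke", and "Fifteen patients will be recruited for a dose escalation trial in 2018". Treatment Doses: "Treatment doses are of stage-wise dose escalation: 2, 4, 8, 16, and 32 million cells/kg". Table 1 places patients 1–3, 4–6, 7–9, 10–12 and 13–15 at these five doses. No untreated or placebo group is described. The only hint of a second arm is one phrase in Overall Plan: "The final follow-up for the 15th patient in the hAEC arm will be done 12 months after cell delivery".
- **Expected comparison.** Results: "It is expected that at the MTD, infarct expansion will be lower than at the preceding doses and in the control group".
- **Only control figure.** Image Analysis, citing an earlier analysis by the same group: "the IER in the control arm occurred in 75% of patients". Imaging Outcomes defines the infarct expansion ratio (IER) as a comparison of follow-up FLAIR volume with initial DWI volume. No threshold is given for expansion to count as having occurred.
- **Anisotropy.** Image Analysis plans to characterise "longitudinal change in the fractional anisotropy (white matter integrity) around the infarct". Results, after naming smaller edema and less infarct expansion, adds that "a decrement in fractional anisotropy volume with dose escalation will provide another assessment of safety and efficacy".

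**The concern.** The abstract makes an MR signal of efficacy a component of the design, and Results says the imaging changes will inform on safety and efficacy. Edema and infarct volume change after stroke without any treatment. With no concurrent comparator, a favourable change cannot be separated from natural course or from differences between the patients in successive cohorts. A reader of the final report could take a lower IER at the MTD as evidence that the cells work, when the comparison named is undefined in one half (the control group) and very imprecise in the other (the preceding doses).

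The anisotropy sentence raises a separate issue. If the measure is anisotropy itself, a fall is loss of white matter integrity, yet the sentence puts it among the hoped-for findings.

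**Working it through.** **1. Reproduce the plan's own figures.** Five doses × 3 patients = 15, the stated sample size. With a target of 0.3 and limits of 0.6 × 0.3 = 0.18 and 1.4 × 0.3 = 0.42, the BOIN boundaries are 0.2365 and 0.3585. Applied to n = 1 to 15, they return the escalation and de-escalation rows of Table 1 exactly. A uniform prior with posterior P(toxicity > 0.3) > 0.95 returns the stopping row. The sizing is therefore sound on its own terms, but it rests on toxicity alone. The document gives no imaging effect size, alpha or power, so two-sided 0.05 and 80% power are assumed below.

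**2. Control group.** Fifteen recruited and fifteen at an hAEC dose leaves 15 − 15 = 0 controls. The only candidate elsewhere is the earlier control arm with its 75%. IER is continuous, so a percentage of patients needs a cut-off, and none is stated. Even if 75% is taken as a fixed rate, three patients say little:
- 0 of 3 with expansion: one-sided p = 0.25³ = 0.0156; exact 95% CI 0 to 1 − 0.025^(1/3) = 0.71.
- 1 of 3: exact 95% CI 0.01 to 0.91, which includes 0.75.
- Chance of seeing 0 of 3 if the true rate is 50%, 37.5% or 25%: 0.5³ = 12.5%, 0.625³ = 24%, 0.75³ = 42%.

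**3. MTD against preceding doses, planned cohorts of three.**

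| Contrast | Smallest two-sided rank-sum p | Standardised difference d for 80% power (t-test) | Power at d = 0.8 |
|---|---|---|---|
| 3 v 3 (one preceding dose) | 2/C(6,3) = 2/20 = 0.10 | 3.07 | 12% |
| 3 v 12 (all four pooled) | 2/C(15,3) = 2/455 = 0.0044 | 1.96 | 21% |

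The t-test non-centrality is d × √(n₁n₂/(n₁ + n₂)). That is 3.07 × √(9/6) = 3.76 on 4 df, and 1.96 × √(36/15) = 3.04 on 13 df. The 3 v 12 row applies only if the MTD is the top dose and every cohort has three patients.

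**4. MTD at the lowest dose.** There is then no preceding dose. How often this happens depends on the DLT rate, which the document does not give. Its 15.7% is 90-day mortality, whereas DLT is any SAE. Simulating the BOIN design (five cohorts of three, flat DLT rate), the lowest dose is selected in 4.5% of trials at a 10% rate, 14% at 15.7% and 43% at 30%. In the same runs at 15.7%, the selected dose has three patients in 48% of trials and six on average. The adaptive design can therefore put more than three patients at the MTD, and the table in step 3 describes the planned layout only.

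**5. Dose trend over all 15.** Reaching p < 0.05 needs |r| ≥ 2.160/√(13 + 2.160²) = 0.51. For 80% power the true correlation must be about tanh((1.960 + 0.842)/√12) = tanh(0.809) = 0.67. This is before the covariate, and uses all 15 patients in one estimate.

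**6. Anisotropy, sections side by side.** Image Analysis: anisotropy stands for white matter integrity, so lower is worse. Results: a decrease in an anisotropy volume appears beside two favourable changes. The sections agree only if the volume is that of tissue with abnormal anisotropy. Neither section says so, and Image Analysis describes change in anisotropy, not a volume.

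**The case against.** The sentence in Results is an expectation about a secondary imaging outcome, not a planned test. Statistical Analysis names descriptive statistics and MTD estimation only, and the primary imaging outcome is presented as a safety measure. This stands: the point concerns what the plan says imaging will show, not an error in the primary analysis or in dose escalation.

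A reader might infer that the efficacy signal is impossible to show. The documents do not support that. The text speaks of preceding doses in the plural. Three against 12 pooled patients can reach p = 0.0044, and a trend over 15 patients or a contrast with a fixed 75% can also reach nominal significance if the effect is very large. The 0.10 floor belongs to a single 3 v 3 contrast, and the MTD may hold more than three patients.

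A reader might also infer that the plan scores white matter loss as benefit. That is the plain reading if anisotropy itself is meant, but the text adds the word volume without defining it, and a shrinking volume of abnormal tissue would be favourable. The reversal is not proven; the ambiguity is.

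Nor is baseline infarct size ignored, since IER divides by the initial DWI volume. Division, however, assumes proportional growth across the eligible range (above 5 and up to 100 mL); a covariate does not.

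Finally, a dose trend has no control either and does not remove the natural-course problem. That is correct, and it is why the trend should carry no efficacy claim.

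**Conclusion.** The point holds in three parts.

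- **Comparator.** The control group named in Results does not exist in this trial. The earlier control arm is the only candidate, is not named there, and supplies a percentage without a cut-off. The reference to an hAEC arm in Overall Plan is not evidence that a control arm was planned.
- **Precision.** On the planned layout, the MTD contrast needs a standardised difference of about 2 (3 v 12) to 3 (3 v 3) for 80% power, at an assumed two-sided 0.05. It has no reference if the MTD is the lowest dose. A signal cannot be reliably shown, and without a concurrent control it cannot be attributed to the cells.
- **Direction.** The anisotropy sentence is either reversed or rests on an undefined measure, and needs correcting or defining in either case.

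The sponsor should settle this before imaging results are read. It does not affect the escalation rules or the MTD estimate.

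**What to change.** 1. Delete the reference to a control group in Results. Alternatively, name the earlier control arm, give the IER cut-off behind its 75%, and label the comparison historical and descriptive.
2. Replace the contrast of the MTD with preceding doses by one exploratory dose trend over all treated patients: log IER on log2(dose), adjusted for log baseline DWI volume, reported as a slope with 95% CI and no claim of efficacy. Analyse edema on its original scale, or with a transformation that admits zero and negative values, because Image Analysis defines it as a difference (FLAIR minus DWI).
3. Define the anisotropy measure and its favourable direction: preserved or higher peri-infarct anisotropy, or a smaller volume of abnormal anisotropy.

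The cost is wording plus one degree of freedom for the covariate; every variable is already collected. The trend remains low-powered (true correlation of about 0.67 for 80% power at n = 15) and does not stand in for a concurrent control.

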## Discussion

If successful, stem cell therapy in the acute phase of ischemic stroke will be transformative for patients who miss out on clot-busting drugs or clot-retrieval therapies, in reducing disability and death. In line with recommendation by the STEPS3 experts, we have avoided including patients who have received TPA or ECR as these therapies would confound the effect of hAECs (8). Apart from allogenic multipotent adult progenitor cells, hAEC is the only other stem cell tested at present in the first 48 h (1, 7). This therapy is attractive as hAECs are readily sourced from healthy term placentae, typically, for logistical ease, after elective cesarean section. There are about 45,000 term elective cesarean section births in Australia alone each year, after which the placenta is discarded. Each term placenta can provide 200–300 million hAECs, sufficient for one stroke patient (70–80 kg) at a dose of 4 million cells per kg. At higher cell doses, pooled cells from two to three placentae would be required for each adult patient. Unlike other forms of stem cell therapy, such as immortalized human neural stem cells derived from 12-week-old human fetuses (18), there are no significant ethical concerns with the collection and therapeutic use of hAECs (25). The risk of tumorigenesis with hAECs is also extremely low due to their lack of expression of telomerase (26).

We have chosen the intravenous route of administration over direct intracerebral delivery as it is less invasive (does not require brain surgery). In our animal experiments, hAECs have action on other organs (such as spleen) affected by stroke. This modulation of the immune response does not require direct intracerebral injection.

From a safety aspect, we have also recently completed a Phase 1 safety trial of intravenously administered hAECs in six preterm infants with established bronchopulmonary dysplasia, using a dose of 1 million cells/kg (ACTRN 12614000174684). No severe adverse events were found to be associated with hAEC treatment. A Phase 1 trial of hAECs in adults with compensated cirrhosis is also underway in our institution (21) (ACTRN12616000437460).

